### Participants

In Norway, specialists in general practice have to renew their clinical specialty every five years. In this renewal process, participation in a number of peer CME group meetings is compulsory, in order to stimulate continuously medical education and reflection. All GPs participating in such peer groups, on average consisting of six to eight peers, located in southern Norway, will be invited to participate in this trial. GPs using one of the four major EPRs (Infodoc^®^, WinMed^®^, ProfDoc Vision^® ^or System X^®^) are eligible for the trial. More than nine out of ten Norwegian GPs use one of these systems routinely during consultations with patients [46].

### Intervention

The intervention has been developed through a process of identifying potential harmful prescriptions to elderly; either as specific drugs and combinations of particular drugs to be avoided due to clinically relevant interactions, or the concurrent use of three or more psychotropic drugs. The identification of suboptimal pharmacological treatments to be targeted in this study, was based on previous research and active reflection and discussions based on own clinical experience from general practice. This process led to the development of a set of prescription QIs (Table 1).

In order to implement rational prescribing patterns, 13 GPs will be recruited as tutors, each with responsibility for the intervention in about three peer groups. Each tutor, named Prescription Peer Academic Detailer (Rx-PAD), will receive a four days' pre-study training program, focusing on safety issues in relation to pharmacological treatment in the elderly, pedagogical intervention techniques, and how to use the data-software for extracting data files from the EPRs. When recruiting the Rx-PADs, emphasis will be laid on economic independence from pharmaceutical manufacturers.

The tailored intervention towards the GPs in the peer CME groups will include two educational outreach visits by one Rx-PAD, discussions within the peer CME group, extraction of prescription data, audit and individual feedback reports, as well as a one day work-shop with all participants, in order to facilitate reflections on personal prescription patterns. Elements in the tailored intervention are summarized in Figure 1.

In the first outreach visit, the main elements of the intervention will be presented, with special emphasis on safer prescription strategies for elderly (≥ 70 years) out-patients, choice of first-line drugs, possible harmful effects of particular drugs, and specific drug combinations to be avoided. During the visit, a software package will be delivered to the participating GPs for installation in own practice computers. This enables data extraction from the preceding 12-month period, which will comprise baseline data used in the study. Prescription data will be collected on diskettes and analyzed by research staff, followed by an individual prescription report which will be mailed to each participant.

The second outreach visit, which will take place within two months after the first one, will focus on the disclosed individual prescription patterns in relation to the explicit recommendations provided during the first meeting. The Rx-PADs will facilitate the discussion within their peer groups, based on the individual feedback reports, enabling participants to compare own prescription patterns with overall averages. This will probably trigger discussion within the peer group, aimed at critical reflection towards own prescription strategies for elderly patients and facilitating disclosure of areas where individual improvements may be desirable.

About three months after the second outreach visit, all participants will be gathered in regional work-shops where rational pharmacological treatment for elderly out-patients ≥ 70 years will be outlined in more depth, on the basis of the baseline prescription data.

Twelve months after the first data extraction, a second data extraction addressing the preceding 12-months prescription patterns, will be made. Each GP will then get a new feedback report revealing before- and after-intervention-data in relation to the QIs and compared with average figures for the total sample. Application will be sent to The Norwegian Medical Association (NMA) to have this educational intervention approved as a so called "clinical theme-course", which will give the participants important CME credit.

### Quality indicators (QIs)

In this study we have developed 14 explicit QIs regarding possible inappropriate prescription patterns to elderly out-patients ≥ 70 years, based on current knowledge and pervious research [15,47-52] (Table 1). The face validity of the QIs will be assessed using a modified three postal round Delphi consensus technique [47,53,54]. The Delphi technique is a structured interactive method involving repetitive administration of anonymous questionnaires, usually across two or three postal rounds [30]. There is limited evidence of the content validity of quality measures derived using the Delphi technique [53,55]. Still, the Delphi procedure has been used for validating the relevance of prescribing indicators [29], i.e. concerning GP's prescribing of non-steroidal anti-inflammatory drugs [47], as well as indicators for patient and general practitioner perspectives of chronic illness [23], and indicators for cardiovascular disease [56]. We will recruit a panel of health professionals (GPs, clinical pharmacologists and geriatricians; about 20 in each group) to rate the face validity of our proposed QIs. Also, the participating GPs will be invited to assess their interpretation of the QIs used in this study by the end of the six-month educational intervention. This will be made by filling in a questionnaire where the relevance of each QI may be scored on a visual-analogue scale.

### Data handling

Software aimed at extracting predefined data sets will be developed for this trial. The software will be compatible with the four electronic patient record (EPR) systems (Infodoc^®^, WinMed^®^, ProfDoc Vision^® ^or System X^®^) used by the waste majority of Norwegian GPs. In addition we will provide technical telephone support during the whole data collection period. The participants will get a deadline for sending their data sets, before they are able to receive an individual feedback report, and the Rx-PAD will remind their group to send data sets before the second peer group meeting.

Data extraction will provide information on contacts with patients and prescriptions issued. Prescription data will be described in terms of The Anatomical, Therapeutic, Chemical (ATC) classification system with Defined Daily Doses (DDDs), in short: the ATC/DDD system [57].

In order to merge prescription data provided by NorPD with data from the EPR systems, the Civil Personal Registration (CPR) number for each patient will be extracted from the EPR. These are the unique identification numbers for Norwegian citizens, and will be deleted from the research database after the record linkage has been performed. The dataset from NorPD will provide data on drugs actually dispensed.

Extracted data from the EPR will be encrypted, stored on a diskette and mailed to the principal researcher. A flow-chart of the data collection is summarized in Figure 2.

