### Outcome measures

Primary outcome measures will be changes in prescription patterns after the tailored educational intervention regarding the listed QIs (Table 1). Post-intervention prescription data will be collected one year after the collection of the baseline prescription data. Prescription patterns in the intervention group will be compared with the non-intervention control group, and with corresponding data (from NorPD) based on a random sample of Norwegian GPs not included in the current trial.

In addition to investigating changes in each QI, we will summarize changes for all QIs (Table 1), in order to give a total sum score for improvement potentials. The difference in total QI sum score between the intervention group and the control group will be a main outcome measure. The QI regarding regular use of the EPR function showing patient's total regular medications will not be included in this sum score. Outcome measures are summarized in Table 2.

It would also be interesting to investigate if this intervention may influence all-over mortality patterns for elderly patients targeted during this intervention as compared to corresponding elderly patients in the control group [44]. By 2006, death data are not yet included in the NorPD, but efforts are currently undertaken to include such data in the NorPD on a regular basis. A possible mortality study has not yet been elaborated in details, but this will be considered.

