### Sample size and statistics

In a pilot study (including 13 physicians) for the present study, the mean number of positive hits on our listed QIs (Table 1) made up 25 hits per 100 elderly patients during the preceding 12 months period. In accordance with this finding, we anticipate an occurrence of inappropriate prescription of about 25 hits per 100 elderly patients in the present study.

Proving a clinical relevant reduction from 25 to 17 hits or less per 100 patients (32% relative reduction), assuming that the prevalence of inappropriate prescriptions in the control group remains constant, will imply a need for 74 peer groups in total (power of 80%; statistical significance level of 5%). This estimation takes into account the need to adjust for intra-cluster correlation, since data within the peer CME groups cannot be assumed to be independent. Furthermore, we assume the average number of GPs per peer CME group to be 7 (allowing for some withdrawals) and that the average number of patients ≥ 70 years per participating GP during the study period will be 165. Based on previous studies [46,58], the intracluster correlation coefficient is assumed to be 0.085, resulting in a variance inflation factor of 99 [59].

We will carry out post-test comparisons between the intervention and control group using cluster-adjusted chi-square and *t*-tests. Analysis of covariance may be used to adjust for imbalance of baseline levels between the intervention- and control-groups [60]. The data set will primarily be analyzed according to the cluster randomization, however, analyzes at physician- and sub-groups of physicians as well as compared to NorPD-data for GPs not participating in the study, will also be performed.

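### Follow-up outcomes for randomised GPs depend on their own EPR extraction, and no registry route is described for those who stop delivering

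*Protocol article*

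**What the plan says.** All references are to the protocol article.

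- **Intervention.** Participants receive the extraction software at the first outreach visit and install it on their own practice computers. The extraction of the previous 12 months supplies the baseline. For follow-up: "Twelve months after the first data extraction, a second data extraction addressing the preceding 12-months prescription patterns, will be made".
- **Data handling.** Encrypted files are posted on diskette. "The participants will get a deadline for sending their data sets, before they are able to receive an individual feedback report", and the tutor reminds the group before its second meeting. For registry linkage, "the Civil Personal Registration (CPR) number for each patient will be extracted from the EPR"; these numbers are deleted once linkage is done.
- **Design.** NorPD is described as a national registry of dispensed prescription drugs, started in 2004, in which the prescribing of GPs outside the trial can be analysed. The same section says that data will be collected for all eligible patients in both arms.
- **Outcome measures.** The intervention arm is compared with the control arm and with "corresponding data (from NorPD) based on a random sample of Norwegian GPs not included in the current trial". The indicator on use of an EPR function is left out of the sum score.
- **Sample size and statistics.** The main analysis is a cluster-adjusted comparison at post-test, with optional covariance adjustment for baseline. On loss of GPs the section says only "we assume the average number of GPs per peer CME group to be 7 (allowing for some withdrawals").

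**The concern.** The trial should estimate the effect of offering the programme to randomised CME groups. That needs a follow-up outcome for the GPs in those groups whether or not they stay engaged. Here the outcome passes through an act of the GP, after allocation, up to a year into the programme. In the intervention arm, delivery is also the condition for the feedback report, so failure to deliver may well go with weak engagement. If non-deliverers differ from deliverers, and do so differently in the two arms, a comparison of delivered data is no longer fully protected by randomisation.

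This cannot be left entirely to an analysis plan. An analysis plan can specify how missing data are handled, but it cannot recover registry data that were never requested or covered by consent.

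**Working it through.** **1. Routes to a follow-up outcome, as described**

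| GP | EPR file | NorPD data |
|---|---|---|
| Randomised, delivers | yes | yes, linked by patient numbers from the EPR |
| Randomised, does not deliver | no | none described |
| Outside the trial | no | yes |

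The second row is the gap. Because the main test is at post-test, the second extraction is the critical one.

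**2. The plan's own sample size**

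Inputs from Sample size and statistics: "Proving a clinical relevant reduction from 25 to 17 hits or less per 100 patients (32% relative reduction"); 7 GPs per group; "the average number of patients ≥ 70 years per participating GP during the study period will be 165"; intracluster correlation 0.085; power 80%; significance level 5%, taken as two-sided.

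- Cluster size: 7 × 165 = 1155. Inflation factor: 1 + (1155 − 1) × 0.085 = 99.09 (stated: 99).
- Uncorrected n per arm: [1.960 × √(2 × 0.21 × 0.79) + 0.842 × √(0.25 × 0.75 + 0.17 × 0.83)]² / 0.08² = 406 after rounding up. With continuity correction: 431.
- Groups per arm: 431 × 99 / 1155 = 36.9, so 37, and 74 in total. This matches the stated figure.

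**3. Does loss of GPs cost power?** (normal approximation without continuity correction)

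- No loss: effective n per arm = 37 × 1155 / 99.09 = 431; power 0.82.
- 40% of GPs lost evenly across groups: cluster size 693, inflation 1 + 692 × 0.085 = 59.82, effective n = 37 × 693 / 59.82 = 429; power still 0.82.
- Whole groups lost, 10/20/30%: power 0.78/0.73/0.68 from 74 groups and 0.81/0.77/0.71 from 80 groups.

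Allowing for withdrawals in the assumed group size therefore deals with precision. It does nothing about selection.

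**4. Possible size of selection, with no true effect**

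The article gives no non-delivery rate, so these values are assumptions. Let a share d of GPs be lost from the intervention arm only, with a hit rate r times that of the GPs who stay, and an all-GP rate of 25. The stayers then show s = 25 / [(1 − d) + d × r].

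| d | r | s | false reduction | share of planned 8 |
|---|---|---|---|---|
| 10% | 1.2 | 24.51 | 0.49 | 6% |
| 10% | 1.5 | 23.81 | 1.19 | 15% |
| 20% | 1.2 | 24.04 | 0.96 | 12% |
| 20% | 1.5 | 22.73 | 2.27 | 28% |
| 30% | 1.2 | 23.58 | 1.42 | 18% |
| 30% | 1.5 | 21.74 | 3.26 | 41% |

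If the same loss falls on the control arm only, the sign reverses. If both arms lose the same share with the same r, both show the same s and the difference is 0.

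**5. A second illustration, with a true effect**

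Suppose deliverers reach 17, non-deliverers in the intervention arm stay at 25, and control loss is unrelated to outcome. The all-randomised mean is (1 − d) × 17 + d × 25, which is 17.8/18.6/19.4 for d = 10/20/30%. The true reduction is 7.2/6.4/5.6 while delivered data show 8.0, an overstatement of 8/7.2, 8/6.4 and 8/5.6, or 11/25/43%. Under the same assumptions, the power of an all-randomised analysis at 74 groups is 0.73/0.62/0.51.

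**The case against.** The strongest reply is that the article states no completer rule. It promises data for all eligible patients and a primary analysis that follows the cluster randomisation. Analysis sets and missing-data rules may sit in a document not shown. This stands: nothing in the text says that GPs without an extraction are excluded. What remains is the data route, which the promise alone does not secure.

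Other points that stand:

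- A missed first extraction does not by itself remove a GP from a post-test comparison. Patient numbers from a first extraction might still allow later NorPD linkage, since the article gives no date for their deletion.
- The deadline sentence governs feedback, and the tutor's reminder concerns the first extraction.
- NorPD holds dispensed drugs; the EPR gives contacts and prescriptions issued. A registry-only analysis needs its own patient denominator. Table 1 is not shown, so it cannot be confirmed that NorPD supports every indicator.
- Controls have their own educational programme and also supply data, so loss may be similar in both arms.
- Telephone support, reminders, planned CME credit and about 80 groups against 74 needed all help. The surplus of groups protects power, not against bias.
- Consent and the secrecy dispensation, as described, cover data extraction and EPR–NorPD linkage. Registry data on GPs who send nothing may need further approval.

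A reader might infer that GPs who disengage are dropped, that the effect is therefore overstated, or that NorPD should replace the EPR as the primary source. The documents support none of these. No exclusion is stated, the direction of any bias depends on loss patterns that are not given, and a change of source would change the measure.

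**Conclusion.** The point holds as a weakness in outcome ascertainment. For a randomised GP who stops delivering, the article describes no follow-up outcome from either source, while it plans registry data for GPs who deliver nothing because they are outside the trial.

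The consequence is a risk of selection bias after randomisation whose size and direction are unknown. Under the assumed one-sided losses of 10–30% and hit-rate ratios of 1.2–1.5, the false difference is 0.5 to 3.3 hits per 100, or 6% to 41% of the planned effect. With balanced loss of similar GPs it is nil. The 11/25/43% overstatement is only an illustration: it rests on assumed non-delivery and on no effect at all in non-deliverers, who could still attend visits and the workshop. Loss of single GPs is not a power problem; loss of whole groups is. The gap should be closed before data requests and consent are final.

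**What to change.** - Request NorPD data by prescriber, for the baseline and follow-up years, for every consenting GP in every randomised CME group, whether or not EPR files arrive.
- State this use in the GP consent, including for GPs who stop taking part, and have the data approvals cover it.
- For all these GPs, analyse the sum-score indicators that NorPD can support, in the groups as randomised, with one denominator of patients aged 70 or over defined identically in both arms. Run this alongside the EPR-linked analysis.
- Report delivery of the first and second extraction by arm, for GPs and for whole groups.

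Cost: a wider registry request and additional consent and approval wording. Because NorPD gives dispensed drugs without EPR contact data, EPR-based detail stays limited to GPs who deliver, and the two analyses will not measure exactly the same thing.

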### Outcome measures

Primary outcome measures will be changes in prescription patterns after the tailored educational intervention regarding the listed QIs (Table 1). Post-intervention prescription data will be collected one year after the collection of the baseline prescription data. Prescription patterns in the intervention group will be compared with the non-intervention control group, and with corresponding data (from NorPD) based on a random sample of Norwegian GPs not included in the current trial.

In addition to investigating changes in each QI, we will summarize changes for all QIs (Table 1), in order to give a total sum score for improvement potentials. The difference in total QI sum score between the intervention group and the control group will be a main outcome measure. The QI regarding regular use of the EPR function showing patient's total regular medications will not be included in this sum score. Outcome measures are summarized in Table 2.

It would also be interesting to investigate if this intervention may influence all-over mortality patterns for elderly patients targeted during this intervention as compared to corresponding elderly patients in the control group [44]. By 2006, death data are not yet included in the NorPD, but efforts are currently undertaken to include such data in the NorPD on a regular basis. A possible mortality study has not yet been elaborated in details, but this will be considered.

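### All 14 quality indicators and their sum score carry primary or main status without ranking, although the trial is sized on total hits alone at a single 5% level

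*Protocol article*

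**What the plan says.** Four places in the protocol article bear on the primary outcome.

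- **Outcome measures** gives primary status in the plural: "Primary outcome measures will be changes in prescription patterns after the tailored educational intervention regarding the listed QIs". It plans to look at each QI and then adds a total: "The difference in total QI sum score between the intervention group and the control group will be a main outcome measure". One indicator is left out of that total: "The QI regarding regular use of the EPR function showing patient's total regular medications will not be included in this sum score".
- **Quality indicators (QIs)** gives the count: "In this study we have developed 14 explicit QIs regarding possible inappropriate prescription patterns to elderly out-patients".
- **Abstract, Methods/design** speaks of one main outcome, the change in the proportions of inappropriate prescriptions, with QIs in brackets. It does not say whether this means each indicator or the total.
- **Sample size and statistics** uses one quantity. In the pilot, "the mean number of positive hits on our listed QIs (Table 1) made up 25 hits per 100 elderly patients". The target is a fall from 25 to 17 per 100, with 80% power at a 5% level. Cluster-adjusted chi-square and t-tests are named. No order of testing and no division of the 5% is given.

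The Design section states one main hypothesis, that the intervention improves prescribing patterns. It does not link that hypothesis to a particular outcome.

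**The concern.** Giving primary status to an outcome is a protocol decision, and the Outcome measures section gives it to the whole set of QIs, with the sum score alongside. The sample size rests on the total alone. The text therefore leaves open what would happen if one or two indicators improved while the sum score did not, or the reverse. Either could be reported as a primary finding.

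Two things are at stake. The 5% level in the sample size calculation governs the trial's conclusion only if the quantity that was sized decides that conclusion. And if the deciding outcome is chosen after the results are known, the choice can follow the results.

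**Working it through.** **1. Reproduce the 74 groups and see which outcome they belong to.**

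Inputs from Sample size and statistics: 25 versus 17 hits per 100 (treated as proportions 0.25 and 0.17), power 80%, level 5%, 7 GPs per group, 165 patients per GP, intracluster correlation 0.085, variance inflation factor 99.

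- Patients per group: 7 × 165 = 1155.
- Inflation factor: 1 + (1155 − 1) × 0.085 = 99.09 (stated: 99).
- Two-sided comparison of two proportions, pooled variance under the null, mean proportion 0.21: n = [1.96 × √(2 × 0.21 × 0.79) + 0.8416 × √(0.25 × 0.75 + 0.17 × 0.83)]² / 0.08² = 406 per arm.
- With continuity correction, n/4 × [1 + √(1 + 4/(n × 0.08))]² = 431 per arm.
- Groups per arm: 431 × 99 / 1155 = 36.9, so 37 per arm and **74 in total**, as stated.

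Other readings do not give 74: two-sided without correction gives 70, one-sided 56, one-sided with correction 60. The stated size is thus a two-sided 5% test of one quantity, total hits.

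**2. False-positive chance if every outcome were tested at 5%.**

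Assumptions, none stated in the article: each outcome is tested at an unadjusted two-sided 5%, and the intervention affects none of them.

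For k independent tests the chance of at least one false positive is 1 − 0.95^k:

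- 13 tests: 48.7%
- 14 tests: 51.2%
- 15 tests: 53.7%

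The 15-test figure is too high for 14 QIs plus their sum, because the sum is built from the QIs. A simulation handles this. It drew 14 test statistics with a common correlation, added the standardised sum of 13 of them, and used 400,000 draws. Thirteen assumes that the indicator excluded from the sum is one of the 14; Table 1 is not visible to confirm this.

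| Assumed correlation between QI test statistics | At least one false positive, either direction | At least one false positive favouring the intervention |
|---|---|---|
| 0 | 52% | 30% |
| 0.1 | 51% | 28% |
| 0.2 | 48% | 25% |
| 0.3 | 44% | 22% |
| 0.5 | 35% | 17% |
| 0.7 | 25% | 12% |
| 0.9 | 14% | 7% |

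Check on the last column: for 14 independent tests, 1 − 0.975^14 = 30%. The benchmark for that column is 2.5%, the one-direction error of a single two-sided 5% test.

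**3. What each remedy would cost.**

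- Sum score as the single primary outcome at 5%: error 5%, and 74 groups as now.
- Fifteen equal primary outcomes with Bonferroni: 0.05/15 = 0.33% each. The same continuity-corrected formula then needs about 132 groups for the total-hits effect. With 74 groups, power for that effect would be about 48%. That power figure is without continuity correction; on the same basis 74 groups give 82% at 5%.

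**The case against.** The strongest reply is that the article already points to the total. It has one main hypothesis, one main outcome in the abstract, one sized quantity, and a sum score defined as a between-group difference. On this view the plural is loose labelling, and any adjustment for multiple tests belongs in an analysis plan that is not shown. Table 2 might also contain a ranking.

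Much of this stands, and it limits what can be claimed. Four stronger inferences are tempting, and the article does not support them.

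- *Each QI is tested at 5%.* The only 5% is in the sample size calculation. The article speaks of investigating each QI and sets no level for doing so. The lack of a stated adjustment is not in itself a fault here.
- *The false-positive chance is about one in two.* That needs nearly independent tests and counts errors in both directions. The QIs come from the same GPs and patients, so correlation is plausible. For false results favouring the intervention, the figure is 30% at zero correlation.
- *No single QI is powered.* The article gives no rates, effects or intracluster correlations for single QIs. It can only be said that their power is not stated.
- *A fall in any one QI makes the trial positive.* The article does not say this. It leaves the deciding result unspecified.

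What the reply does not remove is the wording of the Outcome measures section. It gives primary status to the listed QIs and brings in the sum score as an addition. An analysis plan that named one primary outcome would have to change that text, and a ranking in Table 2 would have to be reconciled with it.

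**Conclusion.** The point holds as one of outcome designation. The article makes changes in all listed QIs primary and the sum score a main outcome, does not rank them in the text that could be read, and sizes the trial on total hits alone. The 74 groups are correct for that single quantity.

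The consequence is conditional. With unadjusted two-sided 5% tests of 14 QIs and the sum, and no true effects, the chance of some false positive is about 52%, 35% and 14% at assumed correlations of 0, 0.5 and 0.9. In favour of the intervention it is about 30%, 17% and 7%. The article gives no correlations, so the range should be quoted and not a single figure. Across these assumed correlations the error exceeds that of a single 5% test.

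**What to change.** - In Outcome measures, name one primary outcome: the between-group difference in total QI sum score, expressed as hits per 100 patients aged 70 or over, without the indicator on the EPR medication-list function (already excluded).
- Make the individual QIs secondary. Either test them by Holm's procedure at 5% only after the sum score is significant, or report them with confidence intervals and no confirmatory claim.
- Align the main-outcome sentence in the abstract, and Table 2 if it differs.
- Confirm that the pilot figure of 25 hits per 100 counts the same indicators as the sum score. The sample size section refers to the listed QIs without repeating the exclusion.

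The cost is wording. If the pilot figure matches, the 74 groups stay unchanged. The downside is that single-QI results lose primary status. The change should be made before outcome data are seen.
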